#### Cost-effectiveness

A cost-effectiveness analysis will be conducted from both provider and patient perspectives. Health outcomes for participants allocated to fMDA and control interventions will be estimated using probabilistic decision tree models, and then compared to determine the incremental effects of fMDA in terms of *P. vivax* incident and prevalent infection averted and disability-adjusted life years (DALY) averted. The results of the trial will be the main source of data on probabilities and complemented with data from the malaria surveillance systems and the scientific literature. DALYs will be estimated using disability weights and life expectancies at death from the WHO life tables. Cost data will include direct and indirect costs of interventions. Costs will be adjusted for inflation and to reflect local government salaries. Deterministic and probabilistic sensitivity analyses will be conducted to understand the effect of parameter uncertainty (effect probabilities and costs) on the incremental cost-effectiveness ratio (ICER) of fMDA, expressed as the cost per *P. vivax* incident infection averted and cost per DALY averted. The analysis will be conducted at the end of the trial after all rounds of fMDA have been completed.

### Ethics

The study will be conducted in accordance with accepted principles on Ethics in Human Experimentation and ICH/GCP. Participants will be compensated a total of 30 soles (~ USD 8.20) per family per visit to compensate them for their time they contribute to the clinical trial away from their jobs. This money will be paid in cash and will be recorded in a document signed by the head of each family acknowledging their compensation. In order to protect the privacy of patients, only authorized study personnel will have access to paper records, and those records will be kept in a locked file at the site facility, Asociación Civil Selva Amazónica. Later they will be transported to the Malaria and Leishmania Unit at the IMTAvH—UPCH in Lima in compliance with established requirements (Reglamento de Ensayos Clínicos). No names will appear on any forms or publications. No information will be shared with anyone else outside of the study without participants’ permission.

### Monitoring and auditing

A fully independent data safety monitoring board (DSMB) will oversee the progress and safety of the study. The board includes a chair with expertise in cluster randomized controlled clinical trials, as Scientist with expertise in malaria, a biostatistician with expertise in clinical trials, and a local Scientist with experience in data and safety monitoring of trials. The DSMB will be included in discussions prior to the start of the trial to review the analysis plan and will meet approximately annually throughout the trial to advise on study progress. The DSMB may decide to withdraw clusters or participants, including cessation of activities for those clusters or participants. Should early evidence of intervention safety problems arise, the DSMB will advise on stopping the study. The study will be halted if > 11/1000 individuals have incidence of any SAE, including by not limited to AHA, related to taking an 8-aminoquinoline. This stopping rule is based on WHO safety threshold guidelines [1].

Both an internal monitor and an external monitor will oversee the clinical trial. The external monitoring agency will conduct regular site visits including to the laboratory. The internal monitor will help develop a detailed monitoring plan including when/how to review patient charts, who will conduct monitoring visits, and who will address findings from monitoring.

The FLAME study team holds regular meetings to communicate about study progress and procedures. The study data management team meets monthly to monitor data quality. The entire study team holds meetings approximately quarterly.

## Discussion

### Potential challenges

A key challenge that may be encountered is ensuring high coverage of the intervention. Community members may be gone for days at a time working in the field, sleep in multiple homes, or live most of the time in the city of Iquitos. To maximize coverage of fMDA, medications will be delivered door-to-door by DOT at times convenient to the participant. Villagers that miss the first round of fMDA in a cycle or become eligible between the first round and second round will be re-considered for fMDA eligibility prior to the subsequent cycle.

Capturing all incident cases of malaria is also challenging. Participants may not seek care when they feel ill or may have an asymptomatic malaria infection. In order to capture as many cases as possible, households will be visited on a monthly basis by the field team to inquire about symptom onset or case diagnosis. Case report forms used to collect these data are include clear, time-anchored prompts that help participants accurately recall events to reduce recall bias. DBS samples will be collected from all study participants at two timepoints (baseline and endline surveys) which may aid in the detection of subclinical infections. Participants will be encouraged to seek care if they feel ill during the study.

The study communities in which we will intervene are dynamic and mobile in nature. The platform QField will be used to update maps of the study communities each visit and participants will be asked during monthly household surveillance if any individuals in their home are new or have left. In this way, population estimates will be maintained as accurately as possible.

## Trial status

Recruitment of study participants began on 14 October 2024 utilizing Spanish protocol version 5.6 from 9 September 2024. Initial enrollment efforts were completed in March 2025; however, participants may be enrolled throughout the trial until the completion of the trial in May 2026.

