### Procedures

#### Enrollment and a baseline assessment

Individual written informed consent will be sought during the baseline survey or during subsequent surveys for new participants. Verbal consent will be requested separately for each subsequent study procedure, including completion of questionnaires, blood testing, and drug administration. Consent for minors less than 18 years of age will be sought from a parent or guardian, and minor assent will also be sought from participants 8–17 years old. Informed consent will be sought in Spanish.

Enrollment and a baseline assessment in consenting individuals will be sought prior to any intervention implementation activities. At the baseline assessment, demographic, epidemiological, and clinical data will be collected. A finger prick will be conducted for rapid G6PD testing using the STANDARD G6PD test (SD Biosensor, Inc., Suwon, South Korea) per manufacturer’s instructions. G6PD status will be categorized as deficient ($$\le$$ 4.0 IU/g Hb), intermediate (4.1–6.0 IU/g Hb), or normal (≥ 6.1 IU/g Hb), which reflect ranges of enzymatic activity below or near normal activity of 9.0 IU/g Hb [31], respectively. As the STANDARD G6PD test includes a hemoglobin (Hb) measurement, this result will also be recorded. Blood from the same finger prick will also be used to generate a dried blood spot (DBS) for malaria molecular testing and G6PD sequencing to identify variants among G6PD deficient and intermediate individuals and 5% of the G6PD normal individuals. For individuals with fever in the past 48 h, microscopy will be performed by health promoters at health establishments, and treatment will be provided per national policy. Current first-line treatment is artesunate-mefloquine for *P. falciparum* and chloroquine (CQ, 10 mg/kg on days 1 and 2, and 5 mg/kg on day 3) plus PQ (0.5 mg/kg/day × 7 days) for *P. vivax* [32].

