#### fMDA in the intervention arm

In the intervention arm, fMDA will be administered over 3 consecutive years. In each cycle, the intervention arm will receive two rounds of fMDA, with each round separated by 2 months and each cycle separated by 9–11 months (Fig. 4). fMDA will be administered by directly observed therapy (DOT) and will target high-risk individuals meeting eligibility criteria detailed in Table 1. These eligibility criteria include being a malaria index case or living in a household within a 200-meter radius of a *P. vivax* index case. The 200-meter radius was selected based on evidence from other cohort studies in the Peruvian Amazon indicating clustering of asymptomatic, submicroscopic infections among neighboring households, generally within 200 meters [33–35]. Index cases will include cases reported in the 2 years prior to the first round of each fMDA cycle detected through passive or active case detection. Individuals with high-risk status will be screened for other inclusion and exclusion criteria for fMDA eligibility.

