#### Identification of index cases and measurement of incidence

Malaria case information is recorded in fever books at health posts, and these cases are reported to the regional level. Index cases from the 2 years prior to trial launch and prior to each cycle of study medication administration will be geo-located prior to that cycle. Index cases also include cases detected during regular interventions by the health system and asymptomatic cases identified during study surveys.

During the trial, any participant with a fever will be instructed to seek medical care. For any new or relapse malaria cases diagnosed, a finger prick will be obtained to collect a DBS before administering treatment. A study team member will also conduct a case investigation (within 48 h of diagnosis) to confirm clinical and demographic details. If a pre-treatment sample was not obtained, study staff will aim to collect a sample from the participant within 3 days. If the new index case is an enrolled participant in the intervention arm, they will be eligible for fMDA at the beginning of the next cycle.

The primary outcome measure of cumulative incidence is the number of incident symptomatic microscopy-confirmed *P. vivax* malaria cases in residents divided by the total population. Cumulative cases will be calculated during the period from trial launch through 1 year after the launch of round 3a of fMDA. The denominator will include all the participants in the study except for those who have withdrawn from the study.

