## Outcomes and measures

### Sample sizes and power calculations

The study is designed to have 80% power to detect at least 68% relative reduction in cumulative *P. vivax* incidence for fMDA versus control over 3 years, with 15 clusters per study arm (mean population per cluster = 251), based on anticipated baseline *P. vivax* API of 65 cases/1000 population for the control arm, a coefficient of variation (*k*) of 0.87 based on past data, and a 0.05 significance level using a two-sided test [69]. As Peru is aiming for malaria elimination, this anticipated effect size is considered necessary and consistent with available evidence [18–20, 70, 71].

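### The stated completion of the trial in May 2026 contradicts a primary outcome window that cannot close before mid-April 2027

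*Protocol article*

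**What the plan says.** The relevant statements in the protocol article are these.

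- Trial status: "Recruitment of study participants began on 14 October 2024"; "Initial enrollment efforts were completed in March 2025"; and "participants may be enrolled throughout the trial until the completion of the trial in May 2026".
- Enrollment and a baseline assessment: "Enrollment and a baseline assessment in consenting individuals will be sought prior to any intervention implementation activities".
- fMDA in the intervention arm: "fMDA will be administered over 3 consecutive years", in cycles of two rounds, "with each round separated by 2 months and each cycle separated by 9–11 months".
- Identification of index cases and measurement of incidence: "Cumulative cases will be calculated during the period from trial launch through 1 year after the launch of round 3a of fMDA".
- Sample sizes and power calculations: power is stated "over 3 years, with 15 clusters per study arm". Study design also calls this a 3-year trial. The Abstract places the three cycles within 2 years.

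Two captions bear on the date. Fig. 2 has study years ending in May. Fig. 4, the study timeline, describes a grant period in June-to-May years and lists an abbreviation for a no-cost extension. Neither figure is available here.

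**The concern.** The end of the primary outcome window is tied to an event, the start of Round 3a, plus a year. The start of recruitment, the order of enrolment and treatment, and the cycle spacing together fix the earliest date on which that window can close. The printed completion date comes before it on every reading.

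What is at stake is the definition of the primary outcome. Follow-up that stopped at the end of May 2026 would miss the year after Round 3a. That year carries the aim, stated under Study design, of showing a sustained effect. On most schedules the third cycle would not have begun either. The endline survey is placed at the close of the final study year, so the timing of the prevalence and seroprevalence outcomes is affected too.

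A smaller point concerns the other end of the window. The article does not tie trial launch to a date. If it meant the first day of recruitment, cases arising before any drug was given would enter the primary count and pull the estimated effect towards no difference.

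**Working it through.** **Inputs.** Recruitment from 14 October 2024; initial enrolment complete in March 2025 (taken as 31 March, since no day is given); completion in May 2026 (taken as 31 May, the latest day). Rounds are 2 months apart and cycles 9 to 11 months apart. The article does not say whether the cycle gap runs from first round to first round (9 to 11 months between a-rounds) or from the second round of one cycle to the first of the next (2 + 9 to 2 + 11, so 11 to 13 months). Both are computed.

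**Time available.** 14 October 2024 to 31 May 2026 is 19.5 months; from 31 March 2025 it is 14.0 months. The shortest window that the spacing allows is 2 × 9 + 12 = 30 months. Annual spacing gives 2 × 12 + 12 = 36 months, which matches the 3-year duration.

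**Dates.** Round 3a = Round 1a + 2 × interval; close = Round 3a + 12 months.

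| Round 1a | Interval between a-rounds (months) | Round 3a | Window closes | Months after 31 May 2026 |
|---|---|---|---|---|
| 14 Oct 2024 | 9 | 14 Apr 2026 | 14 Apr 2027 | 10.4 |
| 14 Oct 2024 | 11 | 14 Aug 2026 | 14 Aug 2027 | 14.5 |
| 14 Oct 2024 | 12 | 14 Oct 2026 | 14 Oct 2027 | 16.5 |
| 14 Oct 2024 | 13 | 14 Dec 2026 | 14 Dec 2027 | 18.5 |
| 31 Mar 2025 | 9 | 30 Sep 2026 | 30 Sep 2027 | 16.0 |
| 31 Mar 2025 | 11 | 31 Jan 2027 | 31 Jan 2028 | 20.0 |
| 31 Mar 2025 | 12 | 31 Mar 2027 | 31 Mar 2028 | 22.0 |
| 31 Mar 2025 | 13 | 31 May 2027 | 31 May 2028 | 24.0 |

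Only the first row has Round 3a before the end of May 2026. Even there Round 3b, two months later, falls on 14 June 2026, so the third cycle is not complete. Working backwards, a close by 31 May 2026 needs Round 1a by 30 November 2023 (31 May 2026 less 30 months), about 10.5 months before recruitment began.

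**Power.** The stated design first, using the usual cluster formula for rates without the added cluster:

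c = (1.96 + 0.84)² × [(λ0 + λ1)/y + k²(λ0² + λ1²)] / (λ0 − λ1)²

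With λ0 = 0.065, λ1 = 0.32 × 0.065 = 0.0208, y = 251 × 3 = 753 person-years and k = 0.87, this gives c = 14.62, or 15 clusters per arm. The plan's figure is reproduced. Power at 15 clusters:

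| Follow-up | Without added cluster | With added cluster |
|---|---|---|
| 36 months | 81.0% | 78.3% |
| 19.5 months | 80.0% | 77.2% |
| 14 months | 79.1% | 76.3% |

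The between-cluster term, 0.87² × (0.065² + 0.0208²) = 0.00353, dwarfs the person-time term, 0.0858/753 = 0.00011. Shortening follow-up therefore matters little to power.

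**Trial launch (illustration on assumed dates).** Suppose counting began on 14 October 2024, Round 1a was on 31 March 2025, and the case rate was constant. Then 5.5 drug-free months precede a window of 30 to 38 months. A true 68% reduction would appear as 0.68 × 30/35.5 = 57% to 0.68 × 38/43.5 = 59%. With launch at Round 1a there is no dilution.

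**The case against.** The strongest reply is that one sentence in Trial status is the outlier. Study design, the fMDA section, the outcome definition and the power statement all describe a longer trial, and annual cycles plus a year give exactly 36 months. May is the end of a study year and of a grant year, and the Fig. 4 caption mentions a no-cost extension. A wrong or pre-extension date is at least as plausible as a shortened trial. This stands. A reader might infer that the trial will in fact stop after one or two cycles and that its primary outcome cannot be observed; the documents do not establish that. The reply explains the conflict but does not remove it, because the sentence refers to completion of the trial itself, not only to the end of enrolment.

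A reader might also infer a loss of power. Planned control-arm cases are 65 × 251 × 15 × 3/1000 = 734, against about 400 (54%) by May 2026, or 285 (39%) counted from the end of March 2025. The calculation above does not support that inference: variation between clusters dominates.

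On trial launch, the two-year look-back for index cases is set before trial launch in one section and before the first round of each cycle in another. That suggests launch lies close to Round 1a. A fixed claim that 68% becomes 59% would therefore go too far; it rests on two dates that the article does not give.

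Lastly, the trial statistician and data analyst are to be blinded to arm, which lessens the worry about a cut-off chosen on the results. The trial is nevertheless open-label, so the order of decisions is worth fixing.

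**Conclusion.** The contradiction holds as printed. No start date or spacing consistent with the article lets the primary window close by May 2026. The shortfall is at least 10.4 months from 31 May 2026, and that minimum needs Round 1a on the first day of recruitment with 9 months between first rounds. It is 14.5 to 24 months if the gap is counted from each second round or if Round 1a follows initial enrolment.

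The consequence, if the date were followed, is to what the primary outcome measures and to the sustained-impact aim, not to formula power. Whether May 2026 is a real limit cannot be settled from the article. The lack of a date for trial launch is a secondary point of conditional size. No view is taken here on which fMDA schedule is right.

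**What to change.** Reconcile Trial status with the cycle spacing and the outcome definition, in one of two ways.

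- If May 2026 is a slip or a superseded grant date, replace it with a completion date at least 12 months after the planned Round 3a. This costs one corrected sentence.
- If May 2026 is a real limit, amend the primary outcome window and state what the shortened trial can and cannot conclude, in particular about the third cycle and sustained impact. Do this before any comparison by arm. This costs a protocol amendment.

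In either case, say from which round the 9-to-11-month gap is counted, and tie trial launch in the primary outcome definition to a stated calendar date. If that date precedes Round 1a, say so and justify counting the cases before treatment. This is a matter of wording only.

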## Data Availability

University of California San Francisco and Universidad Peruana Cayetano Heredia have shared access to the final trial dataset.

## Abbreviations

CQ: Chloroquine
CRCT: Cluster randomized control trial
DALY: Disability-adjusted life year
DOT: Directly observed therapy
DSMB: Data safety monitoring board
FLAME: Focal mass drug administration for vivax malaria elimination
fMDA: Focal mass drug administration
G6PD: Glucose-6-phosphate dehydrogenase
Hb: Hemoglobin
MDA: Mass drug administration
NCE: No-cost extension
PQ: Primaquine
Pv: Plasmodium vivax
TQ: Tafenoquine
WHO: World Health Organization
